
### Protocol

#### Study Objectives

Evaluation of comparative efficacy of Medhya Rasayana (pharmacological) intervention versus Ayurveda nonpharmacological interventions and cognitive behavioral therapy in gadget addiction in children of the age group of 6 to 16 years.

The objectives of this study are listed in Textbox 1.

Primary and secondary objective.

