##### Alternative Hypothesis (H1)

At least 1 intervention among the Medhya Rasayana and Ayurveda nonpharmacological intervention are more effective than the control group in reducing gadget addiction in children.

The purpose of this hypothesis is to determine whether the 3 interventions under comparison in the study differ in their efficacy. If statistically significant differences exist in the outcomes, researchers can ascertain them by testing the null hypothesis against the data gathered during the randomized controlled trial.

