## Methods

### Study Design

A 3-arm superiority randomized controlled trial will be performed. The study flow is depicted in Figure 1. Patients with gadget addiction will be selected from the Kaumarbhritya Outpatient Department of MGACHRC Salod, Wardha as per inclusion criteria mentioned in Textbox 2. During the first visit, Parents will be asked whether they would like to deaddict their child from gadget addiction if they are willing then written informed assent will be obtained from the participants’ guardian. Participants will then complete questionnaires on the internet addiction test scale and digital addiction scale. Furthermore, participants’ social behavior and Prakruti (physical and mental constitution) will be assessed. As well as age, gender, socioeconomic status, and type of gadget he or she is using frequently, and the purpose of gadget use will be assessed. After this period, participants will be randomly allocated to both intervention groups in a 1:1 allocation ratio. After this, Medhya Rasayana will be prescribed to participants in group I according to age-wise doses at a frequency of twice a day for a period of 90 days as mentioned in Table 1. Participants allocated to group II will be counseled regarding the adverse effects of gadget addiction on physical and mental health and advised to follow the following routine daily for a period of 90 days, details of nonpharmacological interventions are described in Tables 1 and 2. Yoga (sun salutations, meditation), Targeted reduction in Gadget use time Padanshik krama, that is, reduce gadget use time by one-fourth part each week. Reduced time will be used for adventure, bravery, cognitive skill-oriented things, sports, and yoga. Patients will be counseled to play indoor and outdoor games daily. Encouragement toward attending social programs whenever required and feasible, encouragement of parent-child relationship by advising parents to spend a minimum of 2 hours of quality time daily with children and to give a reward for not using mobile with encouraging children to learn new things, participate in group activities with peers and teach etiquette. Initial training in sun salutation and the method of meditation will be given to participants and their parents at the time of enrollment. Children will be asked to do the proposed sun salutation and meditation on the assessment day. Participants not responding or not following instructions will be eliminated from the study. Group III will be the external group due to the fact that cognitive behavioral therapy requires trained professionals and there are time and financial constraints as well. Hence, in this published data of previously conducted clinical trials, cognitive behavioral therapy intervention in the management of gadgets or internet addiction will be used for comparison with Medhya Rasayana and Ayurveda nonpharmacological interventions. On the 30th, 60th, and 90th days of treatment, participants will be evaluated using the internet addiction test scale and the *DSM-5* (*Diagnostic and Statistical Manual of Mental Disorders, Fifth Edition*) scale for social behavior. A follow-up will be conducted on the 180th day to determine whether the intervention’s possible effects are lasting.

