
**Figure 1 figure1:**
[figure not shown]
Consolidated Standards of Reporting Trials (CONSORT) flow diagram.

Inclusion and exclusion criteria.Inclusion criteriaParticipants irrespective of gender, religion, and socioeconomic status.Participants affected with gadget addiction as per case definition, that is internet addiction test score: 31-79.Age group between 6-16 years with signs and symptoms of gadget addictions as per *ICD-10* (*International Statistical Classification of Diseases, Tenth Revision*) or 11 as follows.Parents who are willing to provide written informed consent for their children to be included in the study.Exclusion criteriaInternet addiction test score >80.Children aged <6 years and those aged >16 years.Parents who are not willing to provide written informed consent for their children to be included in the study.Children experiencing from behavioral diseases, locomotor diseases, genetic diseases, and systemic disorders.

**Table 1 table1:** Overview of interventions.

	Group P	Group N	Group C
Participants, n	80	80	External group
Name of medication	Medhya Rasayana	Nonpharmacological	Cognitive behavioral therapy
Dosage form	Young’s formula	As per schedule	—^a^
Duration	90 days	90 days	—
Assessment with IAT^b^ scale	0, 30, 60, and 90 days	0, 30, 60, and 90 days	—
Follow up with the IAT scale, digital addiction scale, and *DSM-5*^c^ scale	180th day	180th day	—
Route or mode of administration	Oral	—	—
Anupana	Lukewarm water	—	—

^a^Not applicable.

^b^IAT: internet addiction test.

^c^*DSM-5*: *Diagnostic and Statistical Manual of Mental Disorders* (Fifth Edition).

**Table 2 table2:** Overview of Ayurveda nonpharmacological intervention.

Intervention	Details of method	Duration and frequency
Counseling (Satvavajaya)	Counseling about hazardous effects of mobile and benefits of mobile deaddiction	Fortnight 1 session with parents and child separately
Yoga therapy	Surya Namaskar, Dhyana	Daily
Encouragement for indoor and outdoor games	Patients will be counseled to play indoor and outdoor games daily	Daily for1hour
Encouragement towards attending social programs	Parents will be guided for engagement of children in learning new things, in group activities with peers, etiquette	“Si-opus sit” Whenever required and feasible
Encouragement of parent-child relationship	Parents are advised to spend time with their children. And advised to give a reward for not using mobile to child.	Minimum 2 hours of quality time daily by parents

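### H1 is judged against published CBT results, but no rule ties the source trials to this trial's age limit, IAT window or day-90 time point, and no date fixes the comparator value

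*Protocol article*

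**What the plan says.** Study Design in the protocol article calls the study a three-arm superiority randomised trial, but only P and N are randomised, 1:1. The third group is explained by resources: "Group III will be the external group due to the fact that cognitive behavioral therapy requires trained professionals", with time and money also cited. Its data come from the literature: "published data of previously conducted clinical trials, cognitive behavioral therapy intervention in the management of gadgets or internet addiction will be used for comparison". In Table 1 the participant entry for Group C is "External group", and its duration and IAT times are dashes marked not applicable.

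Under the Alternative Hypothesis, success means that at least one of P and N "are more effective than the control group in reducing gadget addiction in children". Study Objectives describes the target of the comparison as "cognitive behavioral therapy in gadget addiction in children of the age group of 6 to 16 years".

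P and N are defined closely. The inclusion criteria require "internet addiction test score: 31-79" and "Age group between 6-16 years with signs and symptoms of gadget addictions". Table 1 gives 90 days of treatment, with IAT at days 0, 30, 60 and 90. Statistical Analysis lists repeated measures ANOVA and chi-square and says nothing specific about an external comparator.

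**The concern.** The hypothesis is won or lost on the CBT value, and the article's description of its source does not identify one value. Two separate problems follow.

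- **Mismatch.** Published trials may differ from P and N in age eligibility, entry severity and time of measurement. The same therapy then shows a different fall in score, or a different share still addicted, for reasons unrelated to its effect. Therapy is confounded with population.
- **Choice.** With no date for fixing the comparator, nothing in the text prevents the source trials from being selected once P and N scores are known. Selection among several eligible publications favours a finding of superiority.

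**Working it through.** **Inputs.** From Participants: one-sided 5% (1.64), power 80% (0.84), P1 = 0.622 (initial), P2 = 0.362 (after intervention), difference 0.20, 72 per group before dropout. Assumed, because the documents give none: the CBT rates, the number k of published arms, CBT arms of 72, and the between-trial SD.

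**1. The plan's own figure.** With the variance terms bracketed:
(1.64 + 0.84)² × [0.622 × 0.378 + 0.362 × 0.638] / 0.20² = 6.1504 × 0.4661 / 0.04 = 71.66, so 72; and 72 / 0.90 = 80. The figure reproduces. P1 and P2 are before and after proportions, so no CBT rate enters the sample size and none is anchored there.

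**2. Sensitivity to the CBT value.** Take 36.2% still addicted in a trial arm of 72, a CBT arm of 72, and a plain test of any difference:
z = (p_CBT − 0.362) / √{[0.362 × 0.638 + p_CBT(1 − p_CBT)] / 72}

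| Assumed CBT rate | z | Against 1.64 |
|---|---|---|
| 50% | 0.138 / 0.0817 = 1.69 | above |
| 45% | 0.088 / 0.0815 = 1.08 | below |
| 40% | 0.038 / 0.0809 = 0.47 | below |

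Five percentage points in the CBT rate, from 50% to 45%, reverse the conclusion.

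**3. Effect of choosing.** Suppose k published arms of 72 are all truly equal to the trial arm, with no between-trial variance, and the least favourable one is used at nominal one-sided 5%. By simulation the error is about 5% (k = 1), 12% (k = 3) and 17% (k = 5).

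**4. Effect of using an external control at all.** Take one unselected trial and a between-trial SD of 0.2 outcome SD. The sampling variance of the difference is 2/72 = 0.0278, and the test rejects beyond 1.645 × √0.0278 = 0.274.

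- Between-trial variance on the CBT side only: true SD = √(0.0278 + 0.04) = 0.260, and 0.274 / 0.260 = 1.05, so the error is about 15%.
- On both sides: true SD = √(0.0278 + 0.08) = 0.328, and 0.274 / 0.328 = 0.84, so the error is about 20%.

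With k = 3 or 5 at this SD, the error is 35% or 48% (CBT side only) and 39% or 49% (both sides). Only the excess over 15-20% is due to choosing.

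**The case against.** **The age range is already stated.** Study Objectives names 6 to 16 years for the comparison that includes CBT, and the hypotheses speak of children. A reader might infer that the plan takes in any CBT trial, adult samples included. The text does not say that; it simply states no restriction. What stands is that an aim for the comparison is not an eligibility criterion for source trials, and that the IAT window and the time point are not applied to them even as an aim.

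**Post hoc choice is not stated.** A reader might infer that the researchers will pick the trials with P and N results in hand. The article does not say when the CBT data are chosen. The supportable statement is that it gives no date, so the possibility is left open.

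**An article condenses.** Search strategies and extraction sheets normally sit in a fuller document, and their absence here is not itself a fault. This point goes further: the article does say what the control is, the control carries the hypothesis test, and the statement given does not determine it.

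**The numbers are assumptions.** That is correct. In particular, 62.2% must not be read as a CBT result, since Participants gives it as the initial proportion. The larger error rates in step 4 should not be put down to choosing alone.

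**Conclusion.** The point holds as one of design and prespecification. H1 rests on an external CBT value whose source is described only by therapy, condition and publication. Age 6-16 is an aim of the comparison and not a selection rule, no IAT window or time point is applied to the source trials, and no fixing date is given.

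On the assumptions shown, a CBT rate of 50% or 45% puts z at 1.69 or 1.08, on opposite sides of 1.64. Choosing the least favourable of 3 or 5 equal arms takes 5% error to about 12% or 17%. A between-trial SD of 0.2 takes it to about 15-20% with no choosing at all. These figures show how much the open value can matter; they do not predict the trial's result. The documents do not show that selection will occur or that any mismatched trial will be used.

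**What to change.** Before any P or N follow-up score is tabulated, write, date and lock a rule for the CBT source trials:

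- age eligibility within 6-16 years;
- IAT as an outcome;
- IAT entry criteria comparable with 31-79 (a baseline mean inside that range is not enough, since such a trial can still include children scoring 80 or more);
- the result nearest day 90.

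Use all qualifying trials, and fix in advance the number extracted from each. Describe the CBT comparison as non-randomised and external, and include between-trial uncertainty in its interval, because locking the list removes choice but not the error in step 4. If no trial qualifies, make randomised P versus N the confirmatory comparison and restate H0 and H1 accordingly, rather than widening the rule.

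The cost is a literature search, a short dated extraction sheet and a protocol amendment; no added participants are needed for the rule itself. If P versus N becomes confirmatory, the sample size also needs a justification for that contrast, because the present one uses before and after proportions. The main downside is that few or no trials may qualify, which limits or removes the claim of superiority to CBT.

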**Methods:**

A randomized, parallel, triple-arm interventional study will be conducted on diagnosed participants of gadget addiction with an age group of 6- to 16-year-old children, which will be selected and equally distributed in 2 groups. Group P will be given Medhya Rasayana (pharmacological intervention), group N will be nonpharmacological Ayurveda intervention, and group C (cognitive behavioral therapy) will be an external group. The Study duration is 180 days with assessment at baseline, midpoint, and endpoint Appropriate statistical techniques, such as ANOVA and regression analysis, will be used to examine the data and evaluate the efficacy of the 3 groups’ interventions. We will perform subgroup analysis according to initial addiction severity, gender, and age. Primary outcome measures include a reduction in gadget addiction and changes in the psychosocial well-being of participants. Standardized questionnaires and instruments will be used to collect data.

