**Primary objectives**
To evaluate the efficacy of Medhya Rasayana in gadget addiction with an internet addiction test scale, a digital addiction scale, and *DSM-5* (*Diagnostic and Statistical Manual of Mental Disorders* [Fifth Edition]).To evaluate the efficacy of Ayurveda nonpharmacological interventions in gadget addiction with an Internet addiction test scale, a digital addiction scale, and *DSM-5*.To assess the comparative efficacy of 3 therapeutic modalities in the management of gadget addiction by Internet addiction test scale and *DSM-5*.

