**Secondary objectives**
To evaluate the association of gadget addiction with Deha and Manas Prakriti (physical and mental constitution) of the participant with the help of Ayusoft software. Manufactured by C-DAC (Centre for Development of Advanced Computing) To assess the impact of gadget addiction on social relationships and behaviors in the *DSM-5* scale.

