### Assessment of Participants

All participants will be assessed for level of addiction, social behavior, and Prakruti (physical and mental constitution) before initiating the intervention during the study at 0, 30, 60, and 90 days, and on the follow-up day at180 days at Mahatma Gandhi Ayurved Hospital Salod (H). For the assessment of gadget addiction, an internet addiction test scale [31] questionnaire and a digital addiction scale [32] will be used. There are 20 statements on this questionnaire. After carefully reading each statement, participants have to choose the response (0, 1, 2, 3, 4, or 5) that best describes him or her using the 5-point Likert scale. Select the option that most accurately reflects how participants have been spending their time over the past month if 2 options seem to fit equally well. Along with participants, their parents or caretakers will be asked the following question regarding the gadget-addicted behavior of their children and the mean of both scores will be calculated to avoid bias in the study. The social behavior of the patient will be assessed by *DSM-5* [33] criteria on the proposed day Prakruti examination will conducted on the day of initiation of intervention by Ayusoft software [34].

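### No single primary scale or day is fixed, and conflicting visit schedules may leave two scales named as primary without an end-of-treatment value

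*Protocol article*

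**What the plan says.** **Which outcomes are primary.** Textbox 1 opens its primary objectives with "To evaluate the efficacy of Medhya Rasayana in gadget addiction with an internet addiction test scale, a digital addiction scale, and" DSM-5. The second objective repeats the same three scales for the nonpharmacological arm. The third, comparative objective is narrower: "To assess the comparative efficacy of 3 therapeutic modalities in the management of gadget addiction by Internet addiction test scale and" DSM-5, without the digital addiction scale. DSM-5 returns among the secondary objectives: "To assess the impact of gadget addiction on social relationships and behaviors in the" DSM-5 scale. The Abstract describes the primary outcomes differently again: "Primary outcome measures include a reduction in gadget addiction and changes in the psychosocial well-being of participants". The Alternative Hypothesis names neither a scale nor a day.

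**When they are measured.** Treatment lasts 90 days in both randomized arms.
- Study Design has IAT, the digital addiction scale and social behaviour at the first visit. After that: "On the 30th, 60th, and 90th days of treatment, participants will be evaluated using the internet addiction test scale" together with DSM-5. A day-180 follow-up is added, with no scale named.
- Table 1 has IAT alone on days 0, 30, 60 and 90. Its day-180 row reads "Follow up with the IAT scale, digital addiction scale, and" DSM-5.
- Assessment of Participants sets days 0, 30, 60, 90 and 180 for level of addiction and social behaviour. For addiction, an IAT "questionnaire and a digital addiction scale [32] will be used", with no limit on days.
- The Abstract gives three time points over 180 days.

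**Error rate.** The Participants section sets type I error at 5% and type II error at 20%, for one difference in proportions.

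**The concern.** Two problems meet here. The first is practical: staff following Study Design or Table 1 would not give every scale named in the primary objectives on day 90. Part of a primary objective would then have no end-of-treatment data, and no later analysis plan could supply it.

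The second is inferential. Three scales stand side by side with no ranking, the list changes between objectives and Abstract, and no day is named. The analyst could therefore choose the scale and day after seeing the data. The sample size, and the 5% that goes with it, were set for one test.

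**Working it through.** **1. Schedules side by side**

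| Source | Day 0 | Days 30 and 60 | Day 90 | Day 180 |
|---|---|---|---|---|
| Study Design | IAT, digital scale, social behaviour | IAT, DSM-5 | IAT, DSM-5 | scale not named |
| Table 1 | IAT | IAT | IAT | IAT, digital scale, DSM-5 |
| Assessment of Participants | IAT, digital scale, social behaviour | same | same | same |

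These cannot all be followed. What is lost at day 90 depends on which is used:
- Study Design: the digital addiction scale is missing, which affects primary objectives 1 and 2. The comparative objective is intact.
- Table 1: the digital addiction scale and DSM-5 are both missing, which affects all three primary objectives. Read literally, neither scale has a baseline either.
- Assessment of Participants: nothing is missing.

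IAT is the only scale that all three places put on days 0, 30, 60 and 90.

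**2. What the 5% covers**

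Inputs from the Participants section: z-values 1.64 and 0.84, P1 = 0.622, P2 = 0.362, difference 0.20, dropout 10%. The two variance terms are taken as one bracket.
- Variance sum: 0.622 × 0.378 + 0.362 × 0.638 = 0.235116 + 0.230956 = 0.466072
- n = (1.64 + 0.84)² × 0.466072 / 0.20² = 6.1504 × 0.466072 / 0.04 = 71.66, so 72
- With dropout: 72 / 0.9 = 80

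The plan's 72 and 80 reproduce. The value 1.64 is the one-sided 5% point; a two-sided test in the same formula would need 92. So the 5% belongs to one one-sided test of one binary outcome.

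**3. Error if any one scale could count**

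For k independent tests at 5%, the chance of at least one false positive is 1 − 0.95^k. Positive correlation lowers it. The correlations below are assumptions, since the protocol gives none. The correlated values come from a multivariate normal calculation at the one-sided limit.

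| Scales | Independent | Correlation 0.5 | Correlation 0.7 | Correlation 0.9 |
|---|---|---|---|---|
| 2 (comparative objective) | 9.75% | 8.8% | 8.0% | 6.8% |
| 3 (objectives 1 and 2) | 14.3% | 11.8% | 10.3% | 8.0% |

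**4. Cost of keeping several primaries**

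For illustration, a Bonferroni split in the plan's own one-sided formula:
- Two scales (2.5% each): 92 per group, 103 with dropout. Power at 72 is 70%.
- Three scales (1.67% each): 103 per group, 115 with dropout. Power at 72 is 64%.

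**The case against.** The strongest reply concerns the error rate. Inflation needs a rule that success on any one scale is enough, and the protocol states none. If every scale had to succeed, there would be no inflation. The words about at least one in the Alternative Hypothesis refer to interventions, not scales. Multiplicity handling is commonly left to an analysis plan, which is not shown here, and a conflict over visit days does not itself raise type I error. All of this stands. A reader might infer that the 5% is already broken; the documents support only that it is not protected.

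A reader might also take 14.3%, or a larger figure from counting three scales on two days (1 − 0.95⁶ = 26.5%), as the size of the problem. Neither suits the between-group comparison. The comparative objective names two scales, so 9.75% is its limit at one day. The six-test count needs all three scales at day 90, which only Assessment of Participants provides, so it cannot be combined with the complaint that day-90 values are missing. Under Table 1 there would be four tests, at most 1 − 0.95⁴ = 18.5%. Scores from the same children 90 days apart are not independent either, and Study Design gives day 180 a separate purpose: whether effects last.

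One could add that Table 1 is only an overview and the article a condensed text. That would excuse silence. It does not excuse three statements of the schedule that disagree, or a list of primary scales that changes between objectives.

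**Conclusion.** The point holds for the schedule and for the unfixed primary endpoint. Two of the three schedules leave the digital addiction scale without a day-90 value, and one also leaves out DSM-5. Part of the primary objectives could then not be answered at the end of treatment. This rests on reading each section as written, with no assumed figures.

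The point on error rate is conditional. The 5% is unprotected if success on any one scale may count: at most 9.75% for the comparative objective (about 8 to 9% at assumed correlations of 0.7 to 0.5), and at most 14.3% for three scales (about 10 to 12%). These limits assume scales that are independent or positively correlated, each tested one-sided at 5% on one day.

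**What to change.** - State one assessment schedule identically in Study Design, Table 1 and Assessment of Participants: IAT at days 0, 30, 60, 90 and 180; the digital addiction scale and DSM-5 at least at days 0, 90 and 180. Bring the Abstract into line.
- Name IAT at day 90 as the single primary endpoint. It also defines eligibility. Say whether it is analysed as a proportion or a score, in the form that matches the sample size; the present calculation uses a proportion.
- Make the digital addiction scale, DSM-5, psychosocial measures and all day-180 results secondary, with the same list in Textbox 1 and the Abstract.

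The cost is added questionnaires at a visit that already takes place: one scale if Study Design was being followed, two if Table 1 was. Parents or caretakers also answer the addiction questions, so the burden is not the child's alone; the protocol does not give the length of the digital addiction scale. The other scales lose confirmatory status. With the primary endpoint kept as a proportion, 72 per group (80 with dropout) is unchanged.

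Whether the primary contrast is between the two randomized arms or against the external group, as the hypotheses are worded, is a separate matter that this change does not settle.
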